#### Secondary Endpoint Analysis

Abstinence will be self-reported by patients via timeline followback and assessed as the absence of opioids (except buprenorphine) on saliva drug screens. Data on abstinence (binary yes and no) will be evaluated with the 9 possible saliva drug screens and urine drug screen and timeline followback data at weeks 1-8 and week 12. Differences between the treatment arms in abstinence will be assessed with a generalized estimating equation analysis using the binomial abstinence outcome as the dependent variable, assessment time, treatment, and the interaction between assessment time and treatment as fixed effects and subject as a random factor. This generalized estimating equation will be compared to a second generalized estimating equation without a treatment term using a likelihood ratio test to evaluate the impact of treatment. A treatment responder analysis will also be conducted, with a treatment responder defined as someone with ≥80% of all saliva drug screens and urine drug screens and timeline followback reports negative for all nonprescribed opioids over the course of the trial.

Treatment retention will be measured as time to dropout (number of days from baseline to last face to face contact) and analyzed using the Kaplan Meier method followed by a log rank test to compare treatment groups.

Patient assessments of recovery capital (Brief Assessment of Recovery Capital–10) resilience (Connor-Davidson Resilience Scale–10) and severity of co-occurring psychiatric symptoms (Patient Health Questionnaire–8 and Generalized Anxiety Disorder Questionnaire–7) will be evaluated with a repeated measures mixed model in a manner consistent with the primary endpoint.

Participants’ use patterns with PEAR-008 and reSET-O will include total time engaged, number of lessons and chapters completed, number of lessons and chapters repeated, number of completed self-report assessments, and response to notifications. Descriptive statistics of each treatment arm will be summarized and differences between PEAR-008 and reSET-O will be assessed with a *t* test (or its nonparametric alternative if the distributional assumptions are violated).

Treatment motivation and satisfaction will be evaluated based on individual participants’ rating of interest in using (baseline only), ease of use, satisfaction, perceived helpfulness, and likelihood of recommending reSET-O or PEAR-008. Descriptive statistics (mean, median, standard deviation) will be performed on Likert scale and multiple choice items that assess user satisfaction and attitudes about the patient mobile app. Analyses will be conducted on data collected at each assessment point throughout the study, ratings over the course of the study, and for overall user satisfaction as measured at the end of the study.

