**Secondary**			
	To evaluate the impact of PEAR-008 compared to reSET-O on treatment retention	Time to dropout (last contact with a participant)	
	To evaluate the impact of PEAR-008 compared to reSET-O on abstinence from illicit opioids	Abstinence will be defined as abstinence on patient self-reports (via timeline followback) and the absence of nonbuprenorphine opioids on saliva drug screens. Abstinence (binary outcome: yes or no) will be determined 9 times, weekly during weeks 1-8 and at week 12.	
	To evaluate participants’ digital therapeutic use patterns of PEAR-008 compared to reSET-O	Session duration; number of lessons and chapters completed; number of completed self-report assessments; response to notifications	
	To evaluate the impact of PEAR-008 compared to reSET-O on change in psychiatric symptom severity between baseline and follow-up	Depression symptoms with Patient Health Questionnaire–8; Anxiety symptoms with Generalized Anxiety Disorder–7	
	To evaluate the impact of PEAR-008 compared to reSET-O on change in recovery capital and resilience between baseline and follow-up	Brief Assessment of Recovery Capital–10; Connor-Davidson Resilience Scale–10	
	To evaluate participant motivation and satisfaction over time with PEAR-008 compared to reSET-O	Participant surveys administered at baseline, week 4, week 8, and week 12; participant interview at follow-up	
	To evaluate a more global measure of engagement by combining data from secondary endpoints 3-6	A multivariate analysis of variance combining data from secondary endpoints 3-6	

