### Endpoints

#### Primary Endpoint Analysis

Engagement with PEAR-008 and reSET-O will be defined as the number of active sessions per week. A session is defined as a set of in-app events with the same session ID. An active session is any session that contains some active participation in the app such as navigating to a different screen, engaging with a learning module, or responding to a notification. This endpoint was selected to allow a 1:1 comparison of content delivery method (eg, brief chapters vs longer lessons). The number of active sessions per week will be evaluated with a repeated measures mixed model of the form: *Number of Sessions in a Week = Week + Treatment + Week × Treatment + Subject Error + Random Error*. To evaluate the impact of treatment, this repeated measures mixed model will be compared to another of the form: *Number of Sessions in a Week = Week + Subject Error + Random Error* with a likelihood ratio test. The likelihood ratio test will be evaluated using model fit to maximize the log-likelihood.

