#### Exploratory Endpoint Analysis

Data on abstinence (binary—yes and no) will be evaluated at 9 saliva drug screen and timeline followback time points at weeks 1-8 and week 12. The association between abstinence and engagement will be evaluated using a generalized estimating equation model. A given week will be considered negative if a participant has no indication of opioid use on the saliva drug screens or timeline followback. Missing data will be ignored if saliva drug screens or a timeline followback is available for a given time point. In the case where saliva drug screens and timeline followback methods yield data that do not agree, the week will be considered positive.

The relationship between engagement and retention will be assessed using a Cox proportional hazards model with time to dropout as the dependent variable and the number of active sessions as an independent variable. This analysis will be performed separately for each treatment arm.

Patient assessment of skill acquisition (Cognitive Behavioral Therapy Skills Questionnaire) will be evaluated with repeated measures mixed model analysis consistent with the primary endpoint. Results will be presented for the total Cognitive Behavioral Therapy Skills Questionnaire score, the Behavioral Activation Score, and the Cognitive Restructuring score.

Medication adherence will be evaluated using saliva drug screens and, when possible, confirmed by urine drug screen (positive result for buprenorphine and norbuprenorphine). Differences between the treatment arms in medication adherence will be assessed with a generalized estimating equation analysis consistent with the abstinence analysis.

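### The abstinence analysis, and the adherence analysis tied to it, specify a likelihood ratio test between GEE fits with a random subject factor; that test is not defined for GEE, and forcing it can inflate type I error

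*Protocol article*

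**What the plan says.** Under Secondary Endpoint Analysis, the arms are compared on abstinence by a "generalized estimating equation analysis using the binomial abstinence outcome as the dependent variable". The model terms are assessment time, treatment and "the interaction between assessment time and treatment as fixed effects and subject as a random factor". The treatment effect is then judged as follows: "This generalized estimating equation will be compared to a second generalized estimating equation without a treatment term using a likelihood ratio test". Table 1 fixes the repeated structure: "Abstinence (binary outcome: yes or no) will be determined 9 times, weekly during weeks 1-8 and at week 12".

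Under Exploratory Endpoint Analysis, the adherence comparison "will be assessed with a generalized estimating equation analysis consistent with the abstinence analysis".

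The Primary Endpoint Analysis also uses a likelihood ratio test, but between two repeated measures mixed models, and it adds: "The likelihood ratio test will be evaluated using model fit to maximize the log-likelihood". Its reduced model omits both treatment and the week-by-treatment interaction. The abstinence text says only that the treatment term is left out.

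**The concern.** A GEE solves estimating equations for a marginal mean under a working correlation. It specifies no joint distribution for a person's repeated outcomes, so two fits have no likelihoods to compare, and it contains no random effects. Two of the three named features (random subject factor, likelihood ratio test) belong to a generalized linear mixed model. The third (GEE) does not. The wording looks carried over from the primary analysis, where it is legitimate.

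This is not a detail left to a statistical analysis plan. The article states both the model and the test, and they are incompatible. Whoever runs the analysis must depart from the text, and the possible departures give different p-values and, in one case, a different odds ratio. The worst of them takes a log-likelihood that treats up to nine assessments on one person as independent.

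**Working it through.** **The plan's own figure.** The article gives no power or error figure for the abstinence or adherence test. Its sample size statement concerns the primary endpoint, so there is nothing to reproduce here.

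**Inputs from the article.** 130 participants randomised 1:1, hence 65 per arm. Nine assessments, at weeks 1-8 and 12. A model with time, treatment and their interaction. Nominal α 0.05.

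**Assumptions, not in the article.** Exchangeable within-person correlation ρ of 0.3, 0.5 or 0.7, complete data, no treatment effect, and constant marginal abstinence (0.6 and 0.8 in the simulations).

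**Forced test.** Suppose the statistic is twice the difference in working-independence binomial log-likelihoods. With nine equally correlated outcomes, the person-average contrast has its variance multiplied by 1 + 8ρ, and each within-person contrast by 1 − ρ. The multipliers 1 + 8ρ are 3.4, 5.0 and 6.6.

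*(a) Treatment and interaction both dropped.* The large-sample null law is (1 + 8ρ)·χ²₁ + (1 − ρ)·χ²₍df−1₎, compared with the usual χ² critical value.

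| ρ | Categorical time, 9 df (critical value 16.92) | Linear time, 2 df (critical value 5.99) |
|---|---|---|
| 0.3 | 0.082 | 0.220 |
| 0.5 | 0.113 | 0.298 |
| 0.7 | 0.140 | 0.354 |

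A simulation of 5,000 null trials per scenario agrees for 9 df: 0.082, 0.124 and 0.144 at 60% abstinence, and 0.082, 0.115 and 0.146 at 80%.

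*(b) Only the main effect dropped, linear time.* The test then concerns the arm difference extrapolated to time zero. The mean of the nine times is 48/9 = 5.333 and their sum of squares about the mean is 348 − 256 = 92, so mean²/SS = 28.44/92 = 0.309. The naive variance is proportional to 1/9 + 0.309 = 0.420. The true variance is proportional to (1 + 8ρ)/9 + (1 − ρ)(0.309).

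| ρ | True variance | Ratio to naive | P(\|Z\| > 1.96/√ratio) |
|---|---|---|---|
| 0.3 | 0.594 | 1.41 | 0.099 |
| 0.5 | 0.710 | 1.69 | 0.132 |
| 0.7 | 0.826 | 1.97 | 0.162 |

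A smaller simulation (800 null trials per correlation) gave 11%, 12% and 17%.

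*(c) Only the main effect dropped, categorical time.* With the interaction kept, this tests only the week-1 difference. That is one observation per person, so within-person correlation does not enter. The same 800-trial simulation gave about 5%.

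**Coherent alternatives on the same data** (ρ from 0 to 0.7, both abstinence rates). The robust generalized score test for treatment and interaction jointly (9 df) rejected 0.027-0.048 of the time. An unadjusted robust 9-df Wald test, computed on the identity scale, rejected 0.072-0.089, so a Wald version needs a small-sample correction at 65 per arm.

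**Effect measure.** A logistic mixed model gives a subject-specific odds ratio, a GEE a marginal one. By the usual attenuation approximation, log OR(marginal) ≈ log OR(subject) / √(1 + 0.346σ²), with σ² = 3.29ρ/(1 − ρ) for latent-scale correlation ρ. A subject-specific odds ratio of 2.0 then corresponds to about 1.8 at ρ = 0.3 (σ² = 1.41, factor 0.82) and about 1.4 at ρ = 0.7 (σ² = 7.68, factor 0.52). Both are illustrations.

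**The case against.** The strongest reply is that this is a mislabelled logistic mixed model. A random subject factor plus a likelihood ratio test describes one, and it would match the primary analysis. On that reading the test is defined and no inflation of this kind follows. This stands as a limit on the consequence: inflation is one possible outcome, not a necessary one. It does not rescue the text, because GEE is named for both fits and nothing in the article says a mixed model is meant.

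Some stronger readings are tempting and should not be drawn.

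- A reader might infer false positive rates of 29-45%. Those belong to a single treatment term with no interaction: 2·[1 − Φ(1.96/√(1 + 8ρ))] = 0.29, 0.38 and 0.45. The planned model includes the interaction, so these figures are not for the planned test.
- A reader might infer that the test either cannot be run or must give p-values that are too small. The mixed-model route is a third possibility, and case (c) gives about 5% even when the independence likelihood is used.
- A reader might assume that the independence likelihood is the only one software can return. The article does not support that. The check showed only that one common package reports a log-likelihood for a GEE fit, so the forced test is possible in practice.
- A reader might treat abstinence as the leading clinical secondary outcome. The article does not rank the secondary outcomes. It lists retention first in Table 1 and names retention and abstinence together in the Overview.

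It is also fair to say that the separate responder analysis does not rest on this test, and that the test reaches adherence only through the phrase making that analysis consistent with abstinence.

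**Conclusion.** The point holds: as written, the abstinence comparison cannot be carried out, and the adherence comparison inherits the problem. The size of the harm is conditional. It needs a statistic forced from a working-independence likelihood and positive within-person correlation, which is plausible for repeated drug-use status but is not given in the article. It also depends on how time is coded and on which terms are dropped, which the abstinence text leaves open.

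The scope is one secondary and one exploratory analysis. The primary likelihood ratio test compares mixed models fitted by maximum likelihood and is untouched, and the GEE relating engagement to abstinence states no likelihood ratio test. This is a should-fix.

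**What to change.** Choose one method before analysis and write it down.

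1. **Keep the GEE.** Remove the random subject factor. Test treatment and time-by-treatment jointly with a robust generalized score test, or a robust Wald test with a small-sample correction.
2. **Name a logistic mixed model** with a random subject intercept fitted by maximum likelihood. Keep the likelihood ratio test, and say that the odds ratio is subject-specific.

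Under either option, state that the reduced model drops both treatment and its interaction with time, as the primary analysis does, and say whether time is categorical or linear. Apply the same choice to adherence. The cost is a few sentences and standard software, with no change to the data collected or the sample size.

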### Clinical Assessments

#### Abstinence From Opioids and Buprenorphine Adherence

Participant self-report of substance use and medication adherence will be collected within the reSET-O and PEAR-008 apps. In PEAR-008, participants are prompted to report use or abstinence each time they open the app as part of the check-in feature. In reSET-O, participants are prompted to report substance use or abstinence every 72 hours and can choose to self-initiate responses anytime.

Timeline followback will be completed at each virtual study session to assess patient-reported substance use since the time of the last assessment. The timeline followback is a validated calendar-based assessment used to obtain self-reports of amount and frequency of substance use retrospectively, using memory aids to enhance recall (eg, patterns of use, key dates).

Participants will self-administer a 12-panel saliva drug test during video sessions with study staff, who can assist in proper administration in addition to providing high-fidelity confirmatory testing. The 12-panel tests detect the presence of the following drugs: amphetamines, cocaine, cannabis, opioids, methamphetamine, barbiturates, benzodiazepines, buprenorphine, oxycodone, methadone, fentanyl, and alcohol. Saliva drug testing will be performed at the baseline session, once weekly during weeks 1-8 of the treatment phase and at the week 12 follow-up session. Participants will receive drug screening equipment regularly by mail.

When available, results of urine drug screening collected as part of routine care at participating treatment centers will also be used for participants recruited by AREF. All urine drug screen data are collected for clinical purposes and not as a study procedure. Urine drug screen results will be exported from the electronic medical record for inclusion in the study database. These data will be used to evaluate buprenorphine adherence and drug use. Results from additional urine drug screen confirmatory analyses for buprenorphine and norbuprenorphine may be available for some participants. When available, these data will be used to evaluate buprenorphine adherence.

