### Statistical Analysis

All statistical methods will be consistent with the International Conference on Harmonization E9 Guidance [42]. Data will be summarized by treatment group. For baseline, safety, and efficacy outputs a total population will combine both groups. Where appropriate, the data will be summarized by session in addition to treatment group. Baseline, demographic, and efficacy output data will be summarized by intended treatment. Safety output will be summarized by the treatment received.

Every effort will be made to obtain required data at each scheduled evaluation. Missing data will not be imputed. Sensitivity analyses incorporating various imputation assumptions may be performed if missing data exceed 5% of the total possible observations.

Descriptive statistics will be used to describe the population of study participants at the beginning of the study (mean, standard deviation, minimum, 25th percentile, median, 75th percentile, and maximum for continuous data; frequencies and percentages for categorical data). Differences in continuous variables will be summarized with Hedges *g* effect size; differences in categorical variables will be summarized with odds ratios.

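### Read as written, the responder rule pools saliva, urine and self-report results, so without urine data a denied positive week counts half as much as an admitted one, contrary to the plan's own time-point definition of abstinence

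*Protocol article*

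**What the plan says.** The protocol article scores abstinence in three places.

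- **Table 1, secondary objectives.** "Abstinence will be defined as abstinence on patient self-reports (via timeline followback) and the absence of nonbuprenorphine opioids on saliva drug screens". The outcome is binary and is determined at 9 time points (weeks 1 to 8 and week 12). Both sources must be negative.
- **Exploratory Endpoint Analysis.** "In the case where saliva drug screens and timeline followback methods yield data that do not agree, the week will be considered positive". This rule is stated for the association between abstinence and engagement.
- **Secondary Endpoint Analysis, responder definition.** A responder has "≥80% of all saliva drug screens and urine drug screens and timeline followback reports negative for all nonprescribed opioids over the course of the trial". The units counted are screens and reports. No rule combines the sources within a week, and neither of the two rules above is carried over.

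Saliva is tested "once weekly during weeks 1-8 of the treatment phase and at the week 12 follow-up session", after a baseline test. For self-report, "Timeline followback will be completed at each virtual study session". Urine is not a study procedure, and its use is conditional on availability: "results of urine drug screening collected as part of routine care at participating treatment centers will also be used for participants recruited by AREF". On missing data, the Statistical Analysis section states "Missing data will not be imputed".

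**The concern.** Table 1 lets either source alone rule out abstinence at a time point. The responder rule lets the sources offset each other. If saliva is positive and the participant denies use, the week adds one positive and one negative result. If the participant admits use, it adds two positives. A week with admitted use and a negative saliva test is diluted in the same way, so the problem does not depend on treating saliva as the truth.

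Responder status then depends partly on whether use is disclosed. A participant with more positive weeks can be a responder while one with fewer is not. The trial would also report two results on opioid abstinence, the repeated binary analysis and the responder proportion, built on different ideas of an abstinent week.

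**Working it through.** **Inputs from the article**

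- Saliva screens after baseline: 8 weekly + 1 at week 12 = 9. This reproduces the plan's own count: "Data on abstinence (binary yes and no) will be evaluated with the 9 possible saliva drug screens".
- Timeline followback reports: one per study session at the same time points = 9.
- Threshold: 80%.
- Urine results, u: none for STARS participants; an unspecified number for AREF participants. I take u = 0 first, then vary it.
- Complete data, and the baseline screen not counted (consistent with the 9 screens).

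**Formulas**, for k positive weeks and u = 0:

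- Pooled, all denied: (18 − k)/18
- Pooled, all disclosed: (18 − 2k)/18
- By time point, any positive source counts: (9 − k)/9

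The pooled rule needs 0.80 × 18 = 14.4, so 15 negative results. The time-point rule needs 0.80 × 9 = 7.2, so 8 of 9.

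| Positive weeks k | Pooled, all denied | Pooled, all disclosed | By time point |
|---|---|---|---|
| 1 | 17/18 = 94.4%, pass | 16/18 = 88.9%, pass | 8/9 = 88.9%, pass |
| 2 | 16/18 = 88.9%, pass | 14/18 = 77.8%, fail | 7/9 = 77.8%, fail |
| 3 | 15/18 = 83.3%, pass | 12/18 = 66.7%, fail | 6/9 = 66.7%, fail |
| 4 | 14/18 = 77.8%, fail | 10/18 = 55.6%, fail | 5/9 = 55.6%, fail |

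A denied positive week costs 1/18 (5.6 points) and an admitted one 2/18 (11.1 points), so the denied week carries half the weight. The pooled rule tolerates three denied positive weeks but only one admitted week. When every positive week is admitted, the pooled and time-point rules agree, so the gap comes entirely from discordant weeks.

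**Effect of urine (AREF only)**

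- Nine urine results that all agree with saliva: the denier with k = 3 has 3 + 3 = 6 positives, and the discloser with k = 2 has 2 + 2 + 2 = 6. Both score 21/27 = 77.8% and neither is a responder. A denied week then carries two thirds of the weight of an admitted one (2 of 3 results).
- One urine result: the denier with k = 3 scores 15/19 = 78.9% (fail) if it is positive and 16/19 = 84.2% (pass) if it is negative.

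So urine can remove the reversal, and classification then depends on how many routine urine tests a participant had and when.

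**Illustration of scale (assumed inputs, not from the article).** Assume complete data and no urine; mean weekly saliva positivity of 20% to 40%, beta-distributed between participants with parameters summing to 1 or 3; and 25% to 50% of positive weeks denied. The exact beta-binomial calculation gives a pooled responder rate 3.1 to 12.6 percentage points above the time-point rate. Between 4.5% and 31.3% of declared responders fail the time-point rule. At 30% positivity with parameters summing to 3, the time-point rate is 39.6%; the pooled rate is 46.3% with 25% denial and 52.2% with 50% denial. The model omits weeks with admitted use and negative saliva. The table above needs none of these assumptions.

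**The case against.** **The sentence may mean something else.** It could be meant as 80% within each source, or 80% of composite weeks, and an article may leave such detail to the full protocol or SAP. Either alternative removes the reversal: under both, the denier with 3 positive weeks and the discloser with 2 both fail. But the article states neither. Its wording counts screens and reports against one threshold, and a rule stated in that form is not just an omitted detail. If another meaning was intended, the sentence still has to say so.

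**Urine is part of the rule.** This stands as a limit. The reversal holds for STARS participants and for AREF participants without urine data, not for everyone.

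**Bias between arms.** A reader might infer that disclosure will differ by arm because the trial is open-label and the apps prompt differently: at check-in in PEAR-008, every 72 hours in reSET-O. The article does not support this. Those prompts collect in-app reports, whereas the responder rule uses timeline followback, taken on the same session schedule in both arms. Applying 25% denial in one arm and 50% in the other would produce a difference of about 6 points (52.2 − 46.3 = 5.9) with equal use, but nothing in the article gives a denial rate or suggests that it differs. The open-label design would affect self-report under a time-point rule as well.

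**Importance.** The responder analysis is additional and is not listed as an endpoint in Table 1. The main abstinence comparison is the repeated binary analysis, which this does not affect. That limits the severity but does not make the rule right.

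**Conclusion.** The concern holds under the plain reading of the responder sentence. With complete data and no urine results, 3 denied positive weeks of 9 make a responder (83.3%) and 2 disclosed positive weeks do not (77.8%). By the plan's own time-point definition neither reaches 80%. This is exact arithmetic and needs no assumption about how common use or denial is.

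Three limits apply. Urine results at AREF change the weights and can remove the reversal, at the price of a denominator that differs by site and participant. The inflation of 3.1 to 12.6 points is illustrative only. A spurious treatment effect is not demonstrated; what is shown is misclassification of individuals and inconsistency with Table 1. The point should be fixed, but it concerns a supporting secondary analysis and leaves the primary endpoint and the sample size of 130 untouched.

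**What to change.** Replace the responder sentence with a time-point definition, before outcome data are examined:

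- A responder is a participant abstinent at 80% or more of assessed time points (8 of 9 with complete data).
- A time point is assessed if at least one source (saliva, timeline followback, or urine where used) is available. It is abstinent only if every available source is negative; any positive or discordant result makes it non-abstinent.
- A time point with all sources missing never counts as abstinent. It is left out of the denominator, in line with the no-imputation rule, and a sensitivity analysis counts it as non-abstinent. That sensitivity analysis matters because a participant with few assessed time points could otherwise qualify on little data.
- Use one opioid scope. The responder rule refers to nonprescribed opioids and Table 1 to nonbuprenorphine opioids. A prescribed opioid other than buprenorphine would count under one and not the other, so the two must be reconciled.

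The cost is a short paragraph in the protocol or SAP and one extra sensitivity analysis, with no new data. Responder rates will be somewhat lower in both arms than under the pooled rule, to the extent that saliva and self-report disagree.
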